**Safety Observation Indicators:**

Blood routine, liver and kidney function, ANA, electrocardiogram, chest radiography, etc.

**Safety Evaluation:**

1. Nature and frequency of adverse reactions.
2. Clinically significant changes in laboratory tests.

**Clinical Study Plan**

**1. Brief description:**

This trial is an open, multi-center clinical trial to evaluate the efficacy and safety of recombinant tumor necrosis factor receptor:Fc fusion protein (rhTNFR:Fc) combined with methotrexate (MTX) in the treatment of active rheumatoid arthritis.

Studies abroad have shown that etanercept (trade name: Enbrel) has more rapid effect, better curative effect than MTX, and good safety in the treatment of active moderate and severe rheumatoid arthritis. Meanwhile, after 52 weeks of treatment, subjects treated with etanercept combined with MTX showed significant improvement in the Sharp score of joints compared those treated with the single use of MTX. Imaging showed that combined treatment could effectively prevent bone and joint destruction. However, there is still a lack of relevant research of rhTNFR:Fc (trade name: Yisaipu) as etanercept biosimilar in China. The main purpose of this study is to investigate the efficacy of RhTNFR:Fc combined with MTX in the treatment of active rheumatoid arthritis in Chinese population and the effect of long-term treatment on arthrography.

**2. Trial objective:**

Compare the clinical efficacy and the influence on the joint radiology progression between different treatment groups of RhTNFR:Fc combined with MTX and between these groups and the MTX monotherapy.

**3. Trial design:**

A randomized, controlled, open and multi-center clinical study, which is a Phase IV clinical study

**3. Study subjects:**

Rheumatoid arthritis subjects who meet the inclusion/exclusion criteria randomly divided into 3 groups (Group A, Group B and Group C) using centre-stratified block-permuted randomization with 30 patients in each group and 90 patients in total.

4.1 Inclusion criteria:

Only those subjects who meet all of the following conditions could be included in the trial.

1. The subjects diagnosed with rheumatoid arthritis according to the revised 1987 American College of Rheumatology (ACR) Criteria, and with a disease duration of ≥ 6 months.
2. During the screening period and the baseline period, the swollen joint count (SJC) of the subjects should be ≥ 6 (66 joints counted), while the tender joint count (TJC) should be ≥ 8 (68 joints counted); ESR ≥ 28mm/h or CRP ≥ 20 mg/l in laboratory examination; and ≥ 1 bone erosion lesions revealed in X-ray films of both hands/wrists.
3. Subjects aged between 18 and 60 (inclusive) years old;
4. There has been no use of any marketed or non-marketed biological agents for rheumatoid arthritis (focusing on: etanercept, infliximab, adalimumab, tituximab[CD20 McAb], tocilizumab[IL-6 receptor Ab], abatacept[CTLA4-Ig], anakinra[IL-1 antagonist]) before screening;
5. Any DMARDs drugs used other than MTX have been stopped for 4 weeks before the trial; Oral cortical hormones (prednisone ≤ 10 mg/d or its equivalent) and NSAIDs (up to the maximum recommended dose) are allowed, but the dose should be stable for at least 4 weeks before the baseline period;
6. Women of childbearing potential agreeing to take effective methods of contraception during the trial;
7. The urine pregnancy test of women of childbearing age should be negative during screening.
8. Subjects willing to sign the informed consent form (ICF) and comply with the requirements of the study protocol;

4.2 Exclusion criteria: Subjects complying with any of the following conditions should be excluded from the trial.

1. Major surgery (including joint surgery) performed within 8 weeks before screening, or major surgery planned within 6 months after enrollment.
2. Patients with rheumatic autoimmune diseases other than rheumatoid arthritis: including systemic lupus erythematosus (SLE), mixed connective tissue disease (MCTD), scleroderma and polymyositis. However, subjects with Sjogren syndrome are allowed to participate in this trial. If ANA is positive, the possibility of SLE should be excluded based on the clinical conditions and the negative result of the anti-DNA antibody test.
3. Rheumatoid arthritis with wrist X-ray being Stage IV.
4. Patients having suffered or suffering from inflammatory arthritis other than rheumatoid arthritis (such as gout, reactive arthritis, psoriatic arthritis, seronegative spondyloarthropathy, Lyme disease).
5. Patients who have received any investigational drug within 4 weeks before screening (or 5 half-life periods, whichever is the longer).
6. Patients who have undergone any cell elimination therapy, including the investigational drug (e.g. CAMPATH, anti-CD4, anti-CD5, anti-CD3 and anti-CDl9).
7. Patients treated with intravenous gamma globulin, plasma exchange or Prosorba plasma separation exchange within 6 months before the baseline,.
8. Patients who have been injected with cortical hormones intraarticularly or by other means within 4 weeks before the baseline.
9. Patients who have received any vaccine within 4 weeks before the baseline.
10. Patients who have used any alkylating agents, such as cyclophosphamide, chlorambucil or total lymphoid irradiation, within 4 weeks before the baseline.
11. Subjects with severe and uncontrolled cardiovascular diseases, neurological diseases, pulmonary diseases (including obstructive pulmonary disease and interstitial lung disease), nephropathy, liver diseases, endocrine diseases (including uncontrolled diabetes) and gastrointestinal diseases, etc.
12. Patients with uncontrolled disease state, such as asthma, psoriasis, inflammatory bowel disease and other diseases, usually requiring oral administration or injection of cortical hormones to treat recurrence.
13. Patients with known currently active or recurrent bacterial, viral, fungal, mycobacterial diseases or other infectious diseases (including but not limited to tuberculosis and atypical mycobacterial diseases, granulomatous diseases shown by chest X-ray, hepatitis B and C, HIV infection, herpes zoster, but excluding onychomycosis infection), or patients requiring hospitalization and intravenous antibiotic therapy within 4 weeks prior to screening or infected patients requiring oral antibiotic therapy within 2 weeks prior to screening.
14. Subjects with a history of malignant tumors, including solid tumors and hematological malignancies (except for patients with cutaneous basal cell carcinoma that has been excised or cured).
15. Pregnant or lactating (breastfeeding) women.
16. Subjects suffering from neuropathy and other painful diseases that may interfere with pain evaluation.
17. Serum creatinine > 1.5 mg/dl.
18. Alanine aminotransferase (ALT) or aspartate aminotransferase (AST) > 2 x ULN (if ALT or AST is measured to be > 2 x ULN for the first time, sampling should be conducted again during the screening period), or total bilirubin > 1 x ULN (if total bilirubin is measured to be > 1 x ULN for the first time, sampling should be conducted again during the screening period).
19. Platelet count < 100 × 109 /L or WBC < 3 × 109 /L.
20. HBsAg or anti-HCV positive.

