**5. Test method and course of treatment**

5.1 Test method:

The trial is a randomized, controlled, open-label, multicenter clinical study. Qualified subjects after screening will be randomly divided into 3 groups (Groups A, B and C) using centre-stratified block-permuted randomization, with 30 patients in each group and 90 patients in total:

5.2 Drug usage:

1. In MTX therapy, the initial dose is 10mg/ week, which will gradually be increased to 15 mg/ week (in Week 4);
2. At the same time, 25mg of RhTNFR:Fc (trade name: Yisaipu) will be injected subcutaneously each time, twice a week for treatment.
3. The subjects will be treated with the combined use of MTX according to the above regimen until Week 52, and endpoint evaluation will be conducted. The dose of MTX could be reduced for safety reasons. If the subjects could not tolerate the dose reduction, the event could be recorded as an adverse event. After reduction, the dose could be restored to the prescribed dosage when the investigator thinks it is appropriate.
4. Diagram of drug usage:

Group A:

(RhTNFR:Fc + MTX group), 52 weeks; n=30

Group B:

"MTX monotherapy"; n=30

(RhTNFR:Fc + MTX group)

Group C:

"MTX monotherapy"; n=30

Baseline

52 weeks

24 weeks

4 weeks

12 weeks

36 weeks

MTX dose increase stage: MTX will be increased from 10 mg/ week to 15 mg/ week

Note: Folic acid at 5 mg/ week will be given on the Day 2 of MTX administration in the trial.

5.3 Criteria for drug withdrawal:

If one of the following conditions occurs, the investigator may consider drug discontinuation for observation:

1. A serious adverse event occurs, and it has certain relationship with the investigational drug;
2. An adverse drug reaction occurs, and effective remission cannot be achieved after symptomatic treatment;
3. Laboratory tests: transaminase > 3 times the normal value or WBC < 3×109 /L, or PLT < 100×109 /L;
4. The subject has other diseases, and the investigational drug may aggravate the condition.

5.4 Withdrawal from the trial:

For the patients who withdraw during the trial, the investigator must record the reason and date of withdrawal in detail. Patients who may withdraw during the trial can be divided into the following categories:

- 1. Patients found to fail to meet the inclusion/exclusion criteria during the trial;

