**9. Statistical methods:**

9.1 Selection of statistical analysis data:

Intent-to-treat (ITT): all subjects eligible and enrolled after screening and having taken at least one dose of the drug and received at least one post-treatment effectiveness evaluation; LOCF (last observation carry-forward) will be adopted for those subject’s data not observed during the whole treatment course, that is, estimating the missing values of important indicators using the closest observed data. The ITT analysis will be used in this trial.

Safety population: it includes all subjects having taken at least one dose of the drug and received at least one post-treatment safety evaluation.

9.2 Statistics Analysis Plan:

Statistical analysis will be carried out using the SAS statistical analysis software. A sample size of 90 patients was estimated for the open label period with the assumption that mean mTSS CRF was -0.5±1.0 in the MTX plus rhTNFR:Fc group, and 2.5±5.0 in the MTX group at week 52. A sample size of 25 patients per treatment group was calculated to be necessary for more than 80% power to reject the null hypothesis of no difference among the treatment groups with an α of 0•05. Assuming loss of patients, the study required a minimum of 30 patients in each group. Two-sided test will be used for all statistical tests, and the difference tested will be considered as statistically significant if the P value is equal to or less than 0.05. Measurement data will be statistically described using mean±SD (standard deviation). Paired t-test will be used for intra-group differences before and after the treatment. Enumeration data will be statistically described using frequency (constituent ratio).

Dropout analysis: Calculate the dropout rates and the rates of dropout due to AE.

Efficacy analysis: The paired t test or nonparametric test or chi-square test will be used to evaluate the efficacy indexes.

Safety analysis: Calculate the incidence rate of adverse events and tabulate the AEs occurring during the trial, normal/abnormal changes in laboratory findings before and after the trial, as well as relationships of abnormal changes with the investigational drug

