Attachment I: Trial Flow Chart

Attachment II: Health Assessment Questionnaire (HAQ)

Attachment III: Sharp Score Criteria

Attachment IV: Wrist X-ray Staging Criteria for Rheumatoid Arthritis (ACR)

Attachment V: Table of Swollen and Tender Joint Count

**Attachment I:**

**Trial Flow Chart**

| **Work Contents** | **Baseline Period** | **Treatment Period** | | | |
| --- | --- | --- | --- | --- | --- |
| **D-7~0** | **12W±7d** | **24W±7d** | **36W±7d** | **52W±7d** |
| **Informed consent** | **√** |  |  |  |  |
| **Inclusion criteria** | **√** |  |  |  |  |
| **Exclusion criteria** | **√** |  |  |  |  |
| **Medical history collection** | **√** |  |  |  |  |
| **Vital signs** | **√** | **√** | **√** | **√** | **√** |
| **Physical examination** | **√** | **√** | **√** | **√** | **√** |
| **HBs-Ag/HCV-Ab** | **√** |  |  |  |  |
| **Tuberculin test (PPD)** | **√** |  |  |  |  |
| **Chest X ray** | **√** |  |  |  | **√** |
| **Disease status assessment** | **√** | **√** | **√** | **√** | **√** |
| **Routine blood test** | **√** | **√** | **√** | **√** | **√** |
| **Urinalysis** | **√** | **√** | **√** | **√** | **√** |
| **Blood chemistry test** | **√** | **√** | **√** | **√** | **√** |
| **Erythrocyte sedimentation rate (ESR)** | **√** | **√** | **√** | **√** | **√** |
| **C-reactive protein (CRP)** | **√** | **√** | **√** | **√** | **√** |
| **Rheumatoid factor** | **√** |  | **√** |  | **√** |
| **Anti-CCP (2nd Generation) antibody** | **√** |  |  |  |  |
| **Antinuclear antibody (ANA)** | **√** |  | **√** |  | **√** |
| **ECG** | **√** | **√** | **√** | **√** | **√** |
| **X-ray of both hands (including wrist joint)** | **√** |  | **√** |  | **√** |
| **MRI** | **√** |  |  |  | **√** |
| **Medication administration record** |  | **√** | **√** | **√** | **√** |
| **Documentation of concomitant medications** | **√** | **√** | **√** | **√** | **√** |
| **Adverse event evaluation** |  | **√** | **√** | **√** | **√** |
| **Clinical efficacy evaluation** |  | **√** | **√** | **√** | **√** |

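### The MTX comparator mixes patients starting MTX with patients whose disease is active while on it, and Section 9.2 neither separates nor adjusts for this

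*Protocol*

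**What the plan says.** - **Eligibility (Protocol, Section 4.1, item 5).** "Any DMARDs drugs used other than MTX have been stopped for 4 weeks before the trial". MTX is thus exempt from the washout. No inclusion or exclusion criterion requires earlier MTX, forbids it, limits its dose or duration, or defines an inadequate response to it.
- **Stability.** The same item says of oral steroids and NSAIDs that they "are allowed, but the dose should be stable for at least 4 weeks before the baseline period". No such rule is set for MTX.
- **Disease activity (Section 4.1, item 2).** At screening and baseline "the swollen joint count (SJC) of the subjects should be ≥ 6 (66 joints counted), while the tender joint count (TJC) should be ≥ 8", with raised ESR or CRP and at least one erosion, whatever the MTX history.
- **Trial MTX (Section 5.2, item 1).** "In MTX therapy, the initial dose is 10mg/ week, which will gradually be increased to 15 mg/ week (in Week 4". Nothing is said about patients already taking MTX. Item 3 allows later reduction for safety only.
- **Randomisation (Section 5.1).** "using centre-stratified block-permuted randomization, with 30 patients in each group and 90 patients in total". Centre is the only stratum.
- **Objective (Section 2).** The comparison is "between different treatment groups of RhTNFR:Fc combined with MTX and between these groups and the MTX monotherapy".
- **Analysis (Section 9.2).** The planning assumption is "mean mTSS CRF was -0.5±1.0 in the MTX plus rhTNFR:Fc group, and 2.5±5.0 in the MTX group at week 52": one MTX figure for all histories. The efficacy tests named are the paired t test, a nonparametric test and the chi-square test.
- **Baseline records (Attachment I).** The flow chart lists "Medical history collection" and concomitant medications at baseline. Neither is specific to MTX.

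**The concern.** A patient who has never taken MTX and is allocated to Group C receives a new active treatment. A patient who enters with active, erosive disease while on MTX and is allocated to Group C continues a drug under which the disease is still active. If that patient's earlier dose was above 10 mg/week, Section 5.2 as written lowers it at entry; if it was above 15 mg/week, the trial dose stays below the earlier one. Progression on MTX alone may well differ between these two kinds of patient.

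A difference between Groups A and C then averages two effects, and a reader cannot tell which one the result mainly reflects. Group B has an MTX-only phase and carries the same mixture. With 30 patients per group, chance imbalance in prior MTX also adds some noise to the primary comparison that the named tests do not remove.

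**Working it through.** **1. The plan's own sample size.** Inputs from Section 9.2: means −0.5 and 2.5, SDs 1.0 and 5.0, two-sided alpha 0.05.
- Difference = 2.5 − (−0.5) = 3.0. Average variance = (1.0² + 5.0²)/2 = 13, so SD = 3.606.
- n per group = 2 × (1.960 + 0.842)² × 13 / 3.0² = 22.7, so 23.
- At 25 per group, SE = √(26/25) = 1.020, and power = Φ(3.0/1.020 − 1.960) = 83.7% (Welch t: 80.8%).

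The stated 25 per group for more than 80% power is correct and is not disputed. At 30 per group, SE = √(26/30) = 0.93.

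**2. Who can be in Group C.** Reading item 5, item 2 and Section 5.2 together:

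| Pre-trial MTX | Eligible? | What Group C means | MTX at entry |
|---|---|---|---|
| Never | Yes | Starts MTX | 0 to 10 mg/week |
| Current, up to 10 mg/week | Yes, if active | Continues MTX | Same or raised |
| Current, above 10 mg/week | Yes, if active | Continues MTX | Lowered |

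The protocol gives no count for any row.

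**3. Chance imbalance.** The share with prior MTX, p, is not in the protocol; 30–70% is assumed. With X_A and X_C independent Binomial(30, p), a 20-point gap is 6 patients:
- P(|X_A − X_C| ≥ 6) = 15.5% at p = 0.5, and 12.0% at p = 0.3 or 0.7.
- With 25 evaluable per group (5 patients) it is 20.3% and 16.4%.

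**4. How far Group C itself is off.** When two arms of 30 differ by 20 points or more, their average gap from the same exact calculation is about 24 points. By symmetry half falls on each arm, so Group C is about 24/2 = 12 points from its expected share.

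**5. Effect on the Group C mean.** Shift = 0.12 × g, where g is the progression gap between MTX-experienced and MTX-naive patients in Group C (assumed 1 to 3 points):
- g = 1: 0.12, which is 4% of 3.0 and 0.13 SE.
- g = 3 (for example 1.0 and 4.0, averaging the planned 2.5 at p = 0.5): 0.36, which is 12% of 3.0 and 0.39 SE.

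The gap is applied to Group C only. A 3-point gap at p = 0.5 in Group A would alone give an SD of 3 × 0.5 = 1.5, above the 1.0 that Section 9.2 assumes there.

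**6. Precision at stake.** At g = 3 and p = 0.5, prior MTX accounts for 0.25 × 3² = 2.25 of Group C's variance of 25, or 9%. Removing all of it would bring the SE from 0.93 to √((1 + 22.75)/30) = 0.89.

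**The case against.** - **Randomisation deals with prior MTX.** This stands in expectation: the same eligibility and dosing rules apply to all three groups, and chance imbalance is ordinary sampling error already inside the SD of 5.0. A reader might infer systematic bias in favour of the combination; the design does not imply it. But randomisation does not say what the averaged comparison represents.
- **A mixed population fits the objective.** The title and Section 2 ask about active RA, not about naive patients or inadequate responders, and an average effect is a legitimate Phase IV question. This stands. It still helps the reader to see what the average is made of.
- **Sections 4.1 and 5.2 do not contradict each other.** Correct. Item 5 governs washout, 5.2 governs trial dosing, and both can be followed for every patient. What is missing is a statement of how they fit together for someone already on MTX.
- **Adjustment belongs in the SAP.** Partly right; the SAP is not at hand and may add a covariate. However, Section 9.2 itself names unadjusted tests, and a SAP cannot say how current users are handled at entry.
- **Prior MTX is not ignored.** Right as to recording: history and concomitant medications are taken at baseline, so the information can be had.
- **The size is easily overstated.** A reader might pair the 12–16% probability with a full 20-point deviation of Group C, giving 0.20 × 3.0 = 0.6, or 20% of the planned difference. That probability is for two arms differing from each other. For Group C alone to be 20 points off, the chance is 4.3% at p = 0.5 and 2.6% at p = 0.3 or 0.7.

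**Conclusion.** The point holds as one of interpretation and, to a small degree, precision. The protocol lets Group C combine new MTX starters with patients whose disease is active on MTX, leaves the handling of current users unstated, and names tests that neither separate nor adjust for this. In the 12–16% of cases where two arms of 30 differ by 20 points or more, the Group C mean moves by roughly 0.1–0.4 on average, against a planned 3.0 with SE about 0.93. This rests on an assumed 30–70% prior use and an assumed gap of 1–3 points; neither is in the protocol.

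Two further inferences are not supported:
- A reader might infer that the trial contains MTX failures and patients who were stepped down. The text permits both but documents neither: no prior dose, duration, response or count is given.
- A reader might infer that the sample size is too small. If half the patients were naive with two-thirds of the planned effect, and the rest had the full 3.0, power at 25 per group would be about 69%. But the assumed 2.5±5.0 may already describe a mixed population, and the protocol does not say otherwise.

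**What to change.** - Take pre-trial MTX status (never or current, with last dose) from the baseline medical history and concomitant-medication record, with a stated rule for patients who used it and stopped.
- Pre-specify that status as a covariate in the between-group comparisons of Sharp change and ACR response.
- Report A versus C separately by MTX history, as description only.
- State how 4.1 item 5 and 5.2 item 1 fit together for patients already on MTX. The passages need reconciling; no dose or rule is proposed here.
- Keep centre as the only randomisation stratum: 7 centres × 2 MTX categories would make 14 strata for 90 patients.

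The cost is one baseline field, one covariate and one descriptive table, with no extra patients. The downside is imprecision. With half the patients experienced, each subgroup has about 30 × 0.5 = 15 per group, so the table must be labelled descriptive.

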  2. Treatment discontinuation > 4 weeks during the medication due to adverse drug reaction or other reasons (e.g. the treatment has to be discontinued due to occurrence of other disease, migration to other places and loss to follow-up); or within 24 weeks, the accumulated duration of drug discontinuation has exceeded 8 weeks;
  3. Subjects who withdraw the drug by themselves and give up continuing the trial;
  4. Due to serious adverse drug reaction, the drug must be withdrawn in advance.
  5. Those with poor compliance and failing to take the drug according to the schedule or design;
  6. Those with concurrent occurrence of other serious diseases and the investigator considers inappropriate to continue the medication;
  7. Those failing to complete all the examination items as required and thus not evaluable.

5.5 Trial assessments:

The screening visit will be completed within 3 weeks (21 days) before the first administration of the investigational drug. The baseline visit and randomization will be conducted on the day of the first administration, and informal visits will be conducted every 4 weeks to understand the medication and adverse events of the subjects. Formal visits will be conducted every 12 weeks, and the visit results will be recorded. The endpoint visits will be conducted at week 52. In addition to the baseline, the time window for each visit is ±7 days (based on the baseline).

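### The only required pregnancy test is one urine test at screening; none is required on the day of the first dose or during 52 weeks of treatment

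*Protocol*

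**What the plan says.** Three eligibility rules in the protocol deal with pregnancy:

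- Section 4.1, item 7: "The urine pregnancy test of women of childbearing age should be negative during screening". The summary repeats it.
- Section 4.1, item 6 requires agreement to contraception: "Women of childbearing potential agreeing to take effective methods of contraception during the trial".
- Section 4.2, item 15 excludes: "Pregnant or lactating (breastfeeding) women".

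Section 5.5 fixes the timing before treatment: "The screening visit will be completed within 3 weeks (21 days) before the first administration of the investigational drug", and then "The baseline visit and randomization will be conducted on the day of the first administration". On treatment, "informal visits will be conducted every 4 weeks to understand the medication and adverse events of the subjects", with formal visits at Weeks 12, 24, 36 and 52.

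Section 6.2 schedules routine urine examination before treatment and at those four visits. Neither it nor the safety laboratory list in section 6.3 names a pregnancy test. Attachment I has one pre-treatment column, covering Day -7 to Day 0, in which the inclusion and exclusion criteria are ticked. It has no pregnancy-test row at any visit. Sections 5.3 (drug withdrawal) and 5.4 (withdrawal from the trial) do not name pregnancy.

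**The concern.** By the protocol's own rules, pregnancy and trial treatment do not go together. The one test behind those rules is taken before treatment and need not be taken on the day treatment starts. A woman in early pregnancy could pass eligibility on a result some days or weeks old and be dosed. A woman who conceives later could continue on weekly MTX, given in all three groups, and on twice-weekly rhTNFR:Fc (Group A throughout, Group B after its MTX-only period) until the pregnancy is reported or noticed.

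This concerns the safety of participants. Sample size, endpoints and analysis are not touched.

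**Working it through.** No figure in the plan needs reproducing. The check compares the sections on timing and then does calendar arithmetic.

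**Is a dosing-day test implied?** The protocol separates screening from baseline where it wants both. Section 4.1, item 2 reads "During the screening period and the baseline period, the swollen joint count (SJC) of the subjects should be ≥ 6", whereas item 7 names screening only. Section 5.5 places baseline on the day of the first dose. A test on that day is allowed but not required.

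**Age of the result at the first dose**
- Attachment I reading: the criteria are ticked in the Day -7 to Day 0 column, so 0 to 7 days.
- Section 5.5 reading: up to 21 days.

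**Time from that test to Week 52** (52 × 7 = 364 days)
- Attachment I reading: 0 + 364 = 364 to 7 + 364 = 371 days.
- Section 5.5 reading: up to 21 + 364 = 385 days.

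**Doses with no scheduled re-test** (section 5.2)
- MTX, every group: 1 per week × 52 = 52.
- rhTNFR:Fc, Group A: 2 per week × 52 = 104.

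**Scheduled pregnancy tests on treatment:** 0 at the four formal visits, and 0 at the 4-weekly contacts.

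**Gaps if tests are added at Weeks 0, 12, 24, 36 and 52**
- Nominal: 12, 12, 12 and 16 weeks. The longest gap covers 16 MTX doses and, on combined treatment, 16 × 2 = 32 injections.
- Section 5.5 allows ±7 days at each visit except baseline. The gaps then become 11–13, 10–14, 10–14 and 14–18 weeks. The longest runs from Week 35 to Week 53: 18 MTX doses and 36 injections.

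**Number of strips** (upper bounds, counting all 90 patients as women of childbearing potential)
- Five tests each: 5 × 90 = 450.
- Every 4 weeks: 1 + 52/4 = 14 each, and 14 × 90 = 1,260.

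**The case against.** The strongest reply is that nothing here is contradictory. The protocol has an entry test, an exclusion and a contraception requirement. Contraception is the safeguard it chose for the treatment period, and periodic testing would be a further layer. Because Attachment I ticks the eligibility criteria at Day -7 to Day 0, the supported gap before dosing may be a week at most, with 21 days only the outer limit for completing screening. There is other cover as well: the 4-weekly contacts, physical examination at formal visits, withdrawal of patients found not to meet the criteria (section 5.4, item 1), the open list of unexpected events in section 8.3, and congenital malformation as a serious adverse event in section 8.6.

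Much of this stands, and it keeps the point small. It does not close the gap. Even on the shorter reading no dosing-day test is required, and the other provisions act only once a pregnancy or its outcome is known or noticed. Section 5.4, item 1 arguably covers only errors at entry. The SAP, which is not shown, does not explain the omission, because eligibility tests and visit schedules belong in the protocol. Consent pages were removed before review, so instructions to patients on contraception, self-testing or reporting cannot be judged.

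A reader might infer that the exclusion and contraception rules are left without effect. The documents do not support that: the exclusion still operates through its screening test, and contraception does not depend on strips. A reader might also want an expected number of pregnancies. The documents give neither the share of women of childbearing potential nor a conception rate, so no count can be derived.

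**Conclusion.** The point holds as a low-severity safety improvement. One urine test at screening is the only pregnancy test required. Its result may be 0 to 7 days old (Attachment I) or up to 21 days old (section 5.5) at the first dose, and 52 weeks of treatment follow with no scheduled re-test. The 0-to-7-day figure is inferred from a column that has no pregnancy-test row.

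The long intervals to Week 52 mostly reflect the length of the trial and should not be read as a measure of harm. The documents state no fetal risk for either drug, and none is asserted here. The conclusion rests only on the protocol's own exclusion and contraception rules. The dosing-day test is the best-supported part. For testing on treatment, the documents favour no particular interval, and the formal visits are proposed because urine is already collected there.

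**What to change.** 1. Reword section 4.1, item 7 and its summary copy: for women of childbearing potential, the urine pregnancy test must be negative at screening and again on the day of the first dose, before dosing. The second test must use that day's urine, since the pre-treatment column of Attachment I lets the routine sample be up to 7 days old.
2. Add a pregnancy-test row to Attachment I for women of childbearing potential at baseline and Weeks 12, 24 and 36, using the urinalysis sample on treatment. Tick Week 52 as an end-of-treatment check only, since a test there cannot shorten exposure.
3. Add to sections 5.3 and 5.4 that study drugs are stopped on a confirmed positive test. Without this, detection does not secure an end to exposure.

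**Cost:** at most 450 strips, no extra visits, and at most one extra urine sample per woman on the dosing day. A false positive will occasionally need a confirmatory test. Gaps of 12 to 16 weeks remain (up to 18 at the window limits), and within them detection still depends on the 4-weekly contacts. Testing at those contacts would narrow the gaps for at most 1,260 strips; that choice is for the clinicians.
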